### Abstract

#### Objectives

To evaluate the effect of recombinant erythropoietin on hospitalised COVID-19 patients.

#### Trial design

Concealed, randomized, single-blinded, phase 2 controlled clinical trial with two arm parallel-group design of 20 patients allocated with 1:1 ratio and using the placebo in the control group.

#### Participants

This study will be performed at Shahid Mohammadi Hospital in Bandar Abbas, Hormozgan in Iran. All positive (PCR confirmed) COVID-19 patients ≤65 years old who have Hb ≤9 and at least one of the severe COVID-19 symptoms (tachypnea (breathing rate > 30 beats per minute), hypoxemia (O2 ≤93 saturation, the partial pressure ratio of arterial oxygen <300), Lung infiltration (> 50% of lung field within 24 to 48 hours), progressive lymphopenia, LDH >245 U/l, CRP >100) and are willing to cooperate in this project will be included in the study. Patients with a history of coronary heart disease, thrombosis, deep vein thrombosis, chronic lung disease, diabetes mellitus, weakened immune system, end-stage renal disease, liver disease, and patients with a history of taking oral contraceptive pills, systolic blood pressure more than 160 mm Hg, diastolic blood pressure more than 90 mm Hg and age over 65 and erythropoietin above 500 are excluded.

### **Intervention and comparator**

Patients will receive the standard of care (SOC) based on the treatment protocols of the Iranian National Committee of COVID-19 and recombinant erythropoietin (EPREX Manufactured by Johnson and Johnson Pharmaceutical Company) 300 units / Kg or 4000IU as subcutaneous (SQ) injection three times a day for 5 days and simultaneously Enoxaparin 1 mg/kg SQ daily is also taken to prevent thrombosis in the intervention group. Patients' blood pressure, along with other vital signs, are checked regularly and at regular intervals. In the control group, patients received SOC and the placebo (distilled water) is given as a subcutaneous injection three times a day for 5 days We use sterile water for injection (EXIR pharmaceutical company) as the placebo. To the same appearance of the placebo and the recombinant erythropoietin, they are taken in a separate room in the same size syringes and cover with labels before injection.

### **Main outcomes**

The main outcome for this study is a composite endpoint for Patient clinical symptoms (Respiratory rate, Oxygen saturation state and arterial oxygen partial pressure ratio, Lung infiltration status, blood pressure), Laboratory tests (LDH, CRP, Lymphocyte count, Endogenous erythropoietin, and Haemoglobin level). All of these will be assessed at the beginning of the study (before the intervention) and day 5 after the intervention. The study will also evaluate side effects and how to manage them.

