##### Main outcome variables

Patient clinical symptoms, Laboratory examinations of patients and Hemoglobin

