## Primary outcomes

### 1

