#### **Description**

Respiratory rate

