#### **Description**

Oxygen saturation state and arterial oxygen partial pressure ratio

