#### **Description**

Patients' blood hemoglobin levels

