#### **Timepoint**

Start of study (before the intervention), day 5 after the intervention and 2 to 4 weeks after the intervention

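### The protocol gives two incompatible primary endpoints, an undefined composite and a list of eight separate outcomes, and places haemoglobin differently in each

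*Protocol*

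**What the plan says.** The protocol describes its main outcome in three places.

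- **Abstract, Main outcomes.** "The main outcome for this study is a composite endpoint for Patient clinical symptoms", followed by respiratory rate, oxygenation, lung infiltration and blood pressure, and then by "Laboratory tests (LDH, CRP, Lymphocyte count, Endogenous erythropoietin, and Haemoglobin level". All items are to be read before treatment and at day 5. No scoring or combining rule is given.
- **Protocol summary, Main outcome variables.** "Patient clinical symptoms, Laboratory examinations of patients and Hemoglobin". Haemoglobin is again a main outcome, and no composite is mentioned.
- **Registered outcome list.** Under the heading "Primary outcomes" come eight numbered entries, beginning with "Respiratory rate" and "Oxygen saturation state and arterial oxygen partial pressure ratio". Haemoglobin is not among them. It appears as the single entry under Secondary outcomes, "Patients' blood hemoglobin levels", with the time points "Start of study (before the intervention), day 5 after the intervention and 2 to 4 weeks after the intervention".

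The abstract also states that 20 patients are randomised, 10 per arm, and that the principal investigator, care staff, data collectors and outcome evaluators know the allocation.

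**The concern.** A single composite and eight separate primary outcomes are different trials. The first has one test of one score. The second has several tests and needs a rule for what counts as success. The protocol states both and ranks neither above the other.

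Haemoglobin makes this sharper, because whether it helps decide the trial depends on which section is read. The stated aim is recovery from COVID-19. Haemoglobin is the variable that erythropoietin acts on directly, so its place in the primary endpoint affects what a positive result would mean.

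The people who collect and evaluate outcomes know the arm, and the sample is small. Someone who knows the results by arm could therefore settle which text governs, and nothing in the protocol would show that this had happened.

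**Working it through.** **Step 1. Set the texts side by side.**

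| Item | Abstract | Registered list |
|---|---|---|
| Respiratory rate | in composite | primary 1 |
| Oxygen saturation and pressure ratio | in composite | primary 2 |
| Lung infiltration | in composite | primary 3 |
| LDH | in composite | primary 4 |
| CRP | in composite | primary 5 |
| Lymphocyte count | in composite | primary 6 |
| Endogenous erythropoietin | in composite, baseline and day 5 | primary 7, baseline only |
| Blood pressure | in composite, baseline and day 5 | primary 8, baseline and during the 5 treatment days |
| Haemoglobin | in composite, baseline and day 5 | secondary 1, also at 2 to 4 weeks |

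The abstract has nine items in one endpoint. The list has eight endpoints and no composite. As registered, primary 7 has no reading after treatment starts, so seven of the eight can be compared between arms for a treatment effect.

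**Step 2. What the ambiguity could cost in false positives.** The protocol states no error rate, so there is no figure of its own to reproduce. Three assumptions are needed, none of them in the document: each outcome is tested at two-sided 5%, there is no adjustment, and any one significant result counts as success.

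For k independent tests, the chance of at least one false positive is 1 − 0.95^k:

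- k = 7 (the testable registered outcomes): 1 − 0.95^7 = 0.302
- k = 8 (all eight, or the seven with saturation and pressure ratio tested separately): 1 − 0.95^8 = 0.337

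The outcomes are probably positively correlated, which lowers these figures. A simulation of two-sample t-tests with 10 per arm and a common correlation between normal outcomes (40,000 runs) gave:

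| Correlation | k = 7 | k = 8 |
|---|---|---|
| 0 | 0.302 | 0.337 |
| 0.3 | 0.278 | 0.303 |
| 0.5 | 0.234 | 0.255 |
| 0.7 | 0.188 | 0.197 |

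**Step 3. Count only results that favour treatment.** A two-sided 5% test puts 0.025 in the beneficial direction, so with independence:

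- k = 7: 1 − 0.975^7 = 0.162
- k = 8: 1 − 0.975^8 = 0.183

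**Step 4. What keeping all of them as primaries would cost.** Bonferroni gives 0.05/7 = 0.00714 or 0.05/8 = 0.00625 per outcome. With 10 per arm, a two-sided t-test and an assumed 80% power, the detectable difference is 1.32 SD at 0.05. It rises to 1.76 SD at 0.00714 and 1.79 SD at 0.00625.

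**The case against.** The strongest reply is that the abstract is, by its own account (Full protocol section), a short summary, and that the word composite may be used loosely for a set of outcomes. Scoring and multiplicity are commonly left to an analysis plan, which may exist and is not shown. This is also a 20-patient phase 2 trial.

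Part of this stands. The missing 2-to-4-week haemoglobin reading in the abstract may be plain abbreviation. Missing multiplicity wording is not in itself an error of the protocol. The loose reading of composite does not remove the conflict, however. Haemoglobin would still be primary in two places and secondary in a third, and endogenous erythropoietin would still have two schedules. An analysis plan can elaborate a primary endpoint, but it would first have to choose between the two given here.

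A reader might infer four stronger things that the document does not support:

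- *That the trial has a false-positive rate near one in three.* That figure belongs to eight independent, unadjusted two-sided tests with any one sufficing. The protocol states no such rule. The figure counts an outcome measured only at baseline unless another entry is split, and it includes results favouring placebo.
- *That the composite has no direction of benefit.* The severity criteria for entry imply a direction for six of the nine items: respiratory rate, oxygenation, infiltration, lymphocytes, LDH and CRP. What is missing is the combining rule, and a direction for items such as blood pressure and endogenous erythropoietin.
- *That haemoglobin alone would make the trial positive.* This needs a scoring rule and a haemoglobin effect visible by day 5. The protocol gives neither.
- *That no controlled test of the trial's question is possible.* With the analysis plan unseen, this goes too far.

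**Conclusion.** The point holds as a contradiction within the protocol. The primary endpoint is stated in two incompatible ways, the composite version cannot be computed as written, and haemoglobin and endogenous erythropoietin are handled differently between sections. This rests on the text alone and needs no assumption.

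The error rates are illustrations. They hold only if each outcome is tested at two-sided 5%, unadjusted, with any one counting: 30–34% under independence and about 23–26% at correlation 0.5. Counting only beneficial results, they are about 16–18% under independence. A multiplicity rule in an unseen plan could bring them down, but it would not settle which section defines the primary endpoint. Because unblinded staff could settle that after seeing results, it should be resolved before any comparison of arms.

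**What to change.** Before arms are compared, name one primary endpoint and one test, and make the abstract, the protocol summary and the registered list agree. Either of these would do:

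- choose one of the listed severity measures at day 5; or
- keep the composite with a stated scoring rule. One example is a rank-sum score over the six entry severity markers, each in the direction that the entry criteria imply, with rules for patients who die or are discharged before day 5.

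Make the remaining severity measures secondary. Report endogenous erythropoietin as a baseline characteristic and blood pressure under safety. Keep haemoglobin secondary, with its 2-to-4-week reading.

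The protocol describes recruitment as open since August 2020, with outcome evaluators aware of allocation. The change should therefore be recorded as a dated amendment, with a statement that it was made without looking at outcomes by arm.

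The cost is a mid-recruitment amendment to protocol and registry. It needs no extra patients, and the severity measures are already scheduled. A rank score is less directly interpretable than a single measure, so its components should be reported beside it.

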### **Randomisation**

Eligible participants (20) will be randomized in two arms in the ratio of 1: 1 (10 per arm) by permuted block randomization method using online web-based tools. **Blinding (masking)** Patients participating in the study will not be aware of the assignment to the intervention or control group. The principal investigator, health care personnel, data collectors, and those evaluating the outcome are aware of patient grouping.

### **Numbers to be randomised (sample size)**

A total of 20 patients will participate in this study, who are randomly allocated to the 2 arms with a 1:1 ratio; 10 patients in the intervention group will receive SOC and recombinant erythropoietin, and 10 patients in the control group will receive SOC and placebo.

### **Trial Status**

The protocol version is 3.0, approved by the Deputy of Research and Technology and the ethics committee of Hormozgan University of Medical Sciences on 6th June 2020, with the local grant number of 990108. The expected recruitment end date was on 21th December 2020 but since we had a wide and careful exclusion criteria because of the adverse reactions of the medication, the recruitment (for both cases and controls) was not so easy and did not finish on the expected date and we are still recruiting now. Recruitment began on 17th August 2020 and the updated expected recruitment end date is 1st August 2021.

### **Trial registration**

The protocol was registered before starting subject recruitment under the title: Evaluation of the effect of recombinant erythropoietin on the improvement of COVID-19 patients, [IRCT20200509047364N1](https://en.irct.ir/trial/49282), at Iranian Registry of clinical trials (<https://en.irct.ir/trial/49282>) on 2020/08/09.

### **Full protocol**

The full protocol is attached as an additional file, accessible from the Trials website (Additional file 1). In the interest in expediting dissemination of this material, the familiar formatting has been eliminated; this Letter serves as a summary of the key elements of the full protocol.

The study protocol has been reported in accordance with the Standard Protocol Items: Recommendations for Clinical Interventional Trials (SPIRIT) guidelines (Additional file 2).

### **Keywords**

COVID-19, Randomised controlled trial, protocol, recombinant erythropoietin, erythropoietin Phase 2.

### **Declarations**

**Ethics approval and consent to participate**

The protocol was approved by the ethics committee of Hormozgan University of Medical Sciences on 2020/06/06, with the code [IR.HUMS.REC.1399.165](#).

The authors authenticate that this trial has received ethical approval from the appropriate ethical committee as described above. Written prospective informed consent will be obtained from participants before involvement in the trial in the Persian language.

**Consent for publication**

Not applicable

**Availability of data and materials**

The researchers in this study have not yet made a comprehensive decision to share information.

**Competing interests**

The authors declare that they have no competing interests

**Funding**

This trial is supported by the Deputy of Research and Technology of Hormozgan University of Medical Sciences. This sponsor and founder has no role in designing the study, collection, storage, and analysis of information and in preparing the manuscript.

**Acknowledgements**

We are sincerely thankful to the Clinical Research Development Center of Shahid Mohammadi Hospital, Bandar Abbas, Iran for its support.

### Evaluation of the efficacy and safety of recombinant erythropoietin on the improvement of hospitalised COVID-19 patients

#### Protocol summary

##### Study aim

This study aims to investigate the effect of recombinant erythropoietin on the recovery process of COVID-19 patients.

##### Design

concealed, randomized, single blinded, phase 2 controlled clinical trial with two arm parallel group design of 20 patients, using the placebo in the control group.

##### Settings and conduct

This study will be performed at Shahid Mohammadi Hospital in Bandar Abbas. Patients enter the study after obtaining written consent, but will not know which group they belong to.

##### Participants/Inclusion and exclusion criteria

All positive COVID-19 patients who have  $Hb \leq 9$  and at least one of the severe COVID-19 symptoms and are willing to cooperate in this project will be included in the study. Patients with a history of coronary heart disease, thrombosis, deep vein thrombosis, chronic lung disease, diabetes mellitus, weakened immune system, end stage renal disease, liver disease, and patients with a history of taking oral contraceptive pills, systolic blood pressure more than 160 mm Hg, diastolic blood pressure more than 90 mm Hg and age over 65 and erythropoietin above 500 are excluded.

##### Intervention groups

Patients are divided into two groups. In group A, the standard treatment for COVID-19 patients with recombinant erythropoietin is prescribed. In group B, patients receive standard COVID-19 treatment with the placebo.

##### Main outcome variables

Patient clinical symptoms, Laboratory examinations of patients and Hemoglobin

#### General information

##### Reason for update

The expected recruitment end date was on 2020/12/21

but since we had a wide and careful exclusion criteria because of the adverse reactions of the medication, the recruitment (for both cases and controls) was not so easy and did not finish on the expected date and we are still recruiting now. Recruitment began on 2020/8/17 and the updated expected recruitment end date is 2021/8/1.

##### Acronym

##### IRCT registration information

IRCT registration number: **IRCT20200509047364N1**

Registration date: **2020-08-09, 1399/05/19**

Registration timing: **registered\_while\_recruiting**

Last update: **2021-05-26, 1400/03/05**

Update count: **2**

##### Registration date

2020-08-09, 1399/05/19

##### Recruitment status

**recruiting**

##### Funding source

##### Expected recruitment start date

2020-06-21, 1399/04/01

##### Expected recruitment end date

2021-08-01, 1400/05/10

##### Actual recruitment start date

empty

##### Actual recruitment end date

empty

##### Trial completion date

|                                                                                                                                                                                                                                                                                                                                                                                                                                                                                                                                                                                                                                                                                                                                                                                                                                                                                                                                                                                                                                                                                                                                                                                                                                   |                                                                                                                                                                                                                                                                                                                                                                                                                                                                                                                                                                                                                                                       |
|-----------------------------------------------------------------------------------------------------------------------------------------------------------------------------------------------------------------------------------------------------------------------------------------------------------------------------------------------------------------------------------------------------------------------------------------------------------------------------------------------------------------------------------------------------------------------------------------------------------------------------------------------------------------------------------------------------------------------------------------------------------------------------------------------------------------------------------------------------------------------------------------------------------------------------------------------------------------------------------------------------------------------------------------------------------------------------------------------------------------------------------------------------------------------------------------------------------------------------------|-------------------------------------------------------------------------------------------------------------------------------------------------------------------------------------------------------------------------------------------------------------------------------------------------------------------------------------------------------------------------------------------------------------------------------------------------------------------------------------------------------------------------------------------------------------------------------------------------------------------------------------------------------|
| empty                                                                                                                                                                                                                                                                                                                                                                                                                                                                                                                                                                                                                                                                                                                                                                                                                                                                                                                                                                                                                                                                                                                                                                                                                             | sequence information for interventions. (randomization concealment is done by the treatment team without informing the person responsible for admitting patients and the person who prepared the random sequence.)                                                                                                                                                                                                                                                                                                                                                                                                                                    |
| Scientific title
Evaluation of the efficacy and safety of recombinant erythropoietin on the improvement of hospitalised COVID-19 patients                                                                                                                                                                                                                                                                                                                                                                                                                                                                                                                                                                                                                                                                                                                                                                                                                                                                                                                                                                                                                                                                               | Blinding (investigator's opinion)
Single blinded                                                                                                                                                                                                                                                                                                                                                                                                                                                                                                                                                                                            |
| Public title
Effect of erythropoietin on COVID-19                                                                                                                                                                                                                                                                                                                                                                                                                                                                                                                                                                                                                                                                                                                                                                                                                                                                                                                                                                                                                                                                                                                                                                       | Blinding description
In this study, all participants are aware of participating in this study and enter the study with their consent. All participants are unaware of which group of this study they are in and after grouping patients in the groups, Patients receive recombinant erythropoietin in the treatment group and receive a placebo in the control group. The lead researcher, health care personnel, data collection officials, and those who evaluate the outcome are aware of the grouping of patients. Those who prepare the draft of the article are unaware of the groupings if they do not cooperate in the above cases. |
| Purpose
Treatment                                                                                                                                                                                                                                                                                                                                                                                                                                                                                                                                                                                                                                                                                                                                                                                                                                                                                                                                                                                                                                                                                                                                                                                                       | Placebo
Used                                                                                                                                                                                                                                                                                                                                                                                                                                                                                                                                                                                                                                |
| Inclusion/Exclusion criteria
Inclusion criteria:
All definitively positive COVID-19 patients with Hb $\leq$ 9. Having at least one of the severe symptoms of COVID-19, including tachypnea (breathing rate> 30 beats per minute), hypoxemia (O 2 $\leq$ 93 saturation, the partial pressure ratio of arterial oxygen <300), Lung infiltration (> 50% of lung field within 24 to 48 hours), progressive lymphopenia, LDH>245 U/l, CRP>100
Exclusion criteria:
Patients with a history of coagulopathy Patients with a history of thrombosis Patients with a history of deep vein thrombosis Patients with a history of chronic lung disease Patients with a history of diabetes mellitus Patients with weakened immune systems Patients with a history of end stage renal disease Patients with liver disease Patients with a history of taking oral contraceptive pills (OCPs) Patients with systolic blood pressure greater than 160 mmHg Patients with diastolic blood pressure greater than 90 mmHg Patients over 65 years of age Patients with erythropoietin above 500 Patients with a history of myocardial infarction or unstable angina Patients with a history of malignancy | Assignment
Parallel                                                                                                                                                                                                                                                                                                                                                                                                                                                                                                                                                                                                                         |
| Age
To 65 years old                                                                                                                                                                                                                                                                                                                                                                                                                                                                                                                                                                                                                                                                                                                                                                                                                                                                                                                                                                                                                                                                                                                                                                                                     | Other design features                                                                                                                                                                                                                                                                                                                                                                                                                                                                                                                                                                                                                          |
| Gender
Both                                                                                                                                                                                                                                                                                                                                                                                                                                                                                                                                                                                                                                                                                                                                                                                                                                                                                                                                                                                                                                                                                                                                                                                                             | Secondary Ids
empty                                                                                                                                                                                                                                                                                                                                                                                                                                                                                                                                                                                                                         |
| Phase
2                                                                                                                                                                                                                                                                                                                                                                                                                                                                                                                                                                                                                                                                                                                                                                                                                                                                                                                                                                                                                                                                                                                                                                                                                 | Ethics committees
1                                                                                                                                                                                                                                                                                                                                                                                                                                                                                                                                                                                                                  |
| Groups that have been masked

Participant

                                                                                                                                                                                                                                                                                                                                                                                                                                                                                                                                                                                                                                                                                                                                                                                                                                                                                                                                                                                                                                                                                                                                | Ethics committee
Name of ethics committee
Ethics committee of Hormozgan University of Medical Sciences
Street address
Deputy of Research and Technology, Hormozgan University of Medical Sciences, [name]
City
bandar abbas
Province
Hormozgan
Postal code
[name]                                                                                                                                                                                                                                                        |
